The instructions will make clear that participants should feel free to write down stories of negative changes or to say that they did not experience any change at all. Only medical students involved in clinical practice and medical interns (third to seventh year of medical school) will be invited to participate in this part of the RCT.

Methods to maximise completeness and quality of data: The study coordinator and facilitators will be physically present while collecting the data at each time point to ensure the completeness of data. Additionally, we will use several validation options to increase the quality of the data: specific number range, specific character range, date validation, email address format, and prompts that alert participants when they enter incomplete or invalid answers.

In this study, the familiarity of millennial medical students with technology and computer-based education supports using Web-based questionnaires, which reputedly decrease social desirability bias.[40] Assured of anonymity, respondents should be less concerned about what others may think about their responses, including peers and professors.[41] Data reliability in Web-based questionnaires is reportedly equal to or better than traditional paper-based approaches.[42] Examples include data on self-reported perceived health status, oral contraceptive use, and smoking and alcohol use. Web-based questionnaires are also faster to complete and typically cheaper than traditional approaches, making them ideal for our research.

Methods for ensuring secure storage of data: SurveyMonkey and Google responses are stored in a worksheet that can only be accessed through an account login. Data transmission uses Secure Sockets Layer to encrypt information during transport. The data storage is as secure as most other systems that store survey information. After downloading the data, we will delete it from SurveyMonkey and Google Forms. We will be responsible for ensuring the data are securely stored for seven years and then destroyed in accordance with CIET guidelines for security, storage, and eventual destruction of data records.[43]

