### Methods for analyzing data

Primary analysis***:*** using an intention-to-treat approach, we will perform a t-test including 95% confidence intervals to determine the effect of the intervention, including within-group comparisons (baseline and post-intervention I and II) and between-group comparisons (treated versus control post-intervention).

Secondary analysis: we will adjust for sociodemographic baseline variables. We will conduct both a logistic regression and the Mantel-Haenszel procedure, which will allow comparing the results using two different statistical approaches based on different assumptions. Contrary to logistic regression, the Mantel-Haenszel procedure is nonparametric, which makes it free of any statistical assumption and therefore more robust.[44]

Supplementary analysis: both intervention and control arms will engage in group work during the training session. We will use generalised linear mixed modelling (GLMM), paying special attention to a possible cluster enhancement as participants in some study groups generate stronger learning dynamics than others. Additionally, we will follow the methods proposed by [name] and collaborators[24] to conduct probabilistic transitive closure of each CASCADA result chain, which will allow us to explore walks and blocks between intermediate outcomes and to obtain the cumulative net influence. Probabilistic transitive closure is usually conducted on fuzzy cognitive maps where the weights of relationships between concepts are interpreted as probabilities.[45] Every relationship in the map contributes to the summary weight of a walk through a multiplicative function; this approach is appropriate when the number of factors of the model is pre-set.[45]

In our primary analysis, the between-group comparison will yield three *p* values, and the within group-comparison will yield nine *p* values. We will use the Holm procedure to adjust for multiple testing.[46] The Holm method is as robust as the Bonferroni method, but much more powerful.[47]

Non-statistical methods: the students will enter their narratives of change online. Using AtlasTi 8, two research assistants will individually analyze the transcripts following a deductive thematic analysis approach. In deductive analysis, a theory aligned with the researchers’ interest drives the data analysis;[35] we will use the steps described by the CASCADA model to identify themes of change in the stories.

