Missing data: There is no reason a priori to expect differential missing data between game jam and standard lesson groups, since both include a cultural safety educational intervention. We will document missingness and analyze missing data using Amelia II[48] to impute values for missing data with an EM algorithm for the primary outcome. Estimates will reconcile data from ten imputed data sets using Rubin’s approach[49] in the R package Zelig.[50] Additionally, we will provide an attrition diagram[51] (e.g., proportion of participants completing the surveys in each group plotted over time) demonstrating the engagement of participants over time.

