### Ethics

This RCT applies the ethical principles in the Tri-Council Policy Statement[52] and was approved by Institutional Review Board of the McGill’s Faculty of Medicine (approval number A05-B37-17B) and by the Sub-committee for Research of the Faculty of Medicine at *La Sabana* University (approval number 445). We will explain the confidentiality and anonymity mechanisms and the voluntary nature of participation, and obtain informed consent of participants prior to the study.

The facilitators will ensure that each participant has signed the online informed consent before proceeding with any research activity. They will be available to explain the purpose of the study, potential risks and benefits, the confidentiality of responses, and the respondents’ rights to not answer certain questions or to end their participation in the study.

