## Results

Study enrollment began in July 2019. 640 students completed the baseline survey and were randomised. Data collection is expected to be complete by July 2020 and results are expected in October 2020.

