| **Response rates** | Unique site visitor | Repeat visitors will not be excluded. Some students will share their devices with students who do not have access to an electronic device. |
|  | View rate (ratio of unique survey visitors/unique site visitors) | Not available. |
|  | Participation rate (ratio of  unique visitors who agreed to participate/unique first  survey page visitors) | Not available. |
|  | Completion rate (ratio of users who finished the survey/users who agreed to participate) | Not available. |
| **Preventing multiple entries from the same individual** | Cookies used | Repeat visitors will not be excluded. |
|  | IP check | Repeat visitors will not be excluded. |
|  | Log file analysis | Repeat visitors will not be excluded. |
|  | Log file analysis | Repeat visitors will not be excluded. |
|  | Registration | Repeat visitors will not be excluded. |
| **Analysis** | Handling of incomplete questionnaires | Only completed questionnaires will be analyzed. |
|  | Questionnaires submitted with an atypical timestamp | Not applicable |
|  | Statistical correction | Not applicable |

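### The e-survey appendix restricts analysis to completed questionnaires, which conflicts with the intention-to-treat and multiple-imputation plan, and nothing says which rule governs

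*Protocol*

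**What the plan says.** Two parts of the Protocol set rules for the same data.

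- **Methods for analyzing data, on the main comparison:** the text reads "using an intention-to-treat approach, we will perform a t-test including 95% confidence intervals to determine the effect of the intervention".
- **Methods for analyzing data, missing data:** the plan is to use Amelia II to "impute values for missing data with an EM algorithm for the primary outcome". It adds: "Estimates will reconcile data from ten imputed data sets", combined by Rubin's approach. An attrition diagram is also planned.
- **Multimedia Appendix 2 (CHERRIES), Analysis, row on incomplete questionnaires:** "Only completed questionnaires will be analyzed". The row has no exception and no cross-reference to the imputation plan.

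Three other places bear on whether the rule would come into play. The Ethics section gives respondents the right "to not answer certain questions or to end their participation in the study". Data collection methods describes "prompts that alert participants when they enter incomplete or invalid answers", which warn but are not said to force an answer. The Results section reports that "640 students completed the baseline survey and were randomised", so the randomised population was fixed before any post-intervention form was filled in.

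**The concern.** The two rules give different answers to a basic question: whose data, and which data, enter the primary comparison. Intention-to-treat with imputation keeps everyone randomised and uses whatever they supplied. A completed-forms rule keeps only what is complete.

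Completion at the post-session and six-month time points happens after randomisation. If completion decides membership of the analysis set, the arms are compared among students selected by what they did afterwards. A game jam and a poster workshop could differ in how many students stay to the end or answer six months later, so the randomised comparison would no longer be protected. The direction of any resulting bias cannot be predicted.

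With both rules on record, an analyst could also follow either one and cite the Protocol, including after seeing the results.

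**Working it through.** The plan gives no figure on this point to reproduce: neither Sample size nor the Missing data paragraph states a rate of attrition or of incomplete forms. The check is therefore on the text.

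**1. Are both statements in force?** Yes. Neither sits in a change log, and both are written as rules for analysis. No sentence ranks them.

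**2. Will incomplete forms occur?** The plan foresees them. Respondents may leave items blank or stop (Ethics), participants may withdraw at any time (Criteria for discontinuing), and the on-screen prompts alert only. Staff presence at each time point should keep the number down, but nothing makes it zero.

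**3. What follows under each reading of the appendix row?**

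- *Applied per participant.* Anyone without a completed post-intervention form leaves the comparison. This is a completers-only analysis. It contradicts intention-to-treat and leaves the imputation of the primary outcome with nothing to do.
- *Applied per form.* A part-filled form is set aside, that wave counts as missing, and the wave is then imputed. Everyone randomised stays in. But the form is one 30-item instrument: five sociodemographic items, 15 based on the transcultural self-efficacy tool, and a cultural safety part that carries the primary outcome (Data collection methods). So up to 5 + 15 = 20 items lie outside the primary outcome. The figure is up to 20 because the Protocol does not say whether the sociodemographic items are asked again after baseline. One blank among them makes the form incomplete. Fully observed primary-outcome answers would then be deleted and replaced with imputed values.
- *Applied only to the secondary scale.* The Missing data paragraph confines imputation to the primary outcome, so one could suppose that the row covers the rest. The row does not say so, and both scales sit on the same form.

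**4. Result.** Under the first reading the two rules contradict each other. Under the second they can both be obeyed, but only by discarding observed data that the imputation would otherwise use. The third is not written anywhere. No reading leaves the row harmless as it stands.

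**The case against.** The strongest reply is that the row is about submitted questionnaires, not randomised people. Students who miss the session or do not respond at six months submit no form, so a row on incomplete forms does not address them. The Missing data paragraph does, and it is the more specific text for the primary outcome, whereas the appendix is a brief reporting checklist. Differential absence on the day is also less likely than it might seem: the Discussion says students will know only which auditorium to attend, and both arms last eight hours. The Missing data paragraph sees no prior reason for missingness to differ by arm.

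Most of this stands. A reader might infer from the appendix that the primary analysis is bound to shrink to completers. The documents do not support that: it is one reading of the row, and the form-level reading allows absent waves to be imputed.

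Two things survive. The form-level reading still deletes observed primary-outcome answers because of blanks elsewhere, and the Protocol never says that the Missing data paragraph takes precedence. Masking of the allocation before the session also does not cover leaving during it or failing to answer six months later.

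**Conclusion.** The conflict is real and should be settled before outcomes are compared by arm. Its consequence depends on which reading is followed: a completers-only primary analysis with possible bias of unknown sign, or needless loss of observed primary-outcome data. The conclusion rests on the Protocol text alone and needs no assumption about attrition.

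The size of the effect is unknown. A reader might set the planned 400 against the 640 randomised, infer that 1 − 400/640 = 37.5% would be excluded, and conclude that two-sided power at d = 0.25 would fall from 0.88 (320 per arm) to 0.70 (200 per arm). The arithmetic is right, but the inference is not supported, for two reasons.

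- The 400 is a recruitment target. No source makes it a count of completers.
- The comparison sets no missing data against 37.5% missing. The effect of the rule is the difference between completers and imputation at the same missingness. As a rough guide, suppose 200 of 320 per arm are observed and the baseline score is the predictor, with correlation r. Then 1/n_eff ≈ (1 − r²)/200 + r²/320. For an assumed r of 0.3 this is 0.00455 + 0.00028, so n_eff is about 207 and power about 0.72. For r of 0.7 it is 0.00255 + 0.00153, so n_eff is about 245 and power about 0.79. Even at that unsupported level of loss, the rule itself would account for roughly 0.02 to 0.09 of power, not 0.18.

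The case for the change therefore rests on keeping the randomised population and the observed data, not on a power figure.

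**What to change.** Replace the entry on incomplete questionnaires in Multimedia Appendix 2 with wording such as:

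> All randomised participants are analysed in the arm assigned. Answers in partly completed questionnaires are kept, and missing primary-outcome items or waves are multiply imputed as in the Missing data section. A completers-only analysis is a sensitivity analysis.

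This makes the Missing data paragraph the governing rule and covers both part-filled and absent forms. Details of the imputation model can stay in the statistical analysis plan. The change is one checklist entry and uses a method already planned. The only downside is a little extra analysis work, for handling part-filled forms and running the sensitivity analysis.
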